##### Alternative incentives

2.12.4.2.

The second additional outcome analysis will focus on participants who declined participation but indicated that specific alternative incentives might have increased their likelihood of taking part. Each alternative incentive option will be represented as a binary variable indicating whether that option was endorsed. Descriptive statistics will summarize endorsement frequencies, and graphical displays (e.g., bar charts) will be used to compare the distribution of endorsed options across incentive conditions.

Separate logistic regression models will be fitted for each alternative incentive option, with incentive condition (reference: no incentive) as the main predictor. Odds ratios (ORs) and 95% CIs will be reported, and FDR adjustment will be applied across the set of alternative-incentive models to control for multiple testing.

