It is also important that recruitment strategies are feasible to implement at scale and under practical resource constraints. Evidence from survey methodology suggests that monetary incentives generally increase response rates more than non-monetary incentives, that prepaid incentives often outperform promised incentives, and that money may be more effective than vouchers or lotteries, although prepaid incentives may be difficult to administer in web-based surveys or recruitment contexts (24, 25). At the same time, lottery-based incentives are commonly used within EMA studies to sustain participant engagement after enrolment, as they provide a salient reward while lowering expected marginal costs (19). Whether such incentives also influence individuals' initial decisions to participate, however, remains less clear.

Non-financial strategies may also encourage participation, particularly in community-based research where reciprocity and shared benefit—such as providing feedback on study findings—may motivate engagement. Behavioral theories suggest that different incentives may appeal to different motivations, including financial rewards, topic relevance, or perceived community benefit (26, 27). However, there is limited empirical evidence on whether such non-financial incentives are effective in improving participation in EMA studies.

To address this evidence gap, this study will evaluate the effectiveness of two scalable incentive strategies—a lottery-based financial incentive and a community-framed non-financial incentive—in encouraging invitation-stage willingness to participate in a future EMA study among an urban neighbourhood population. A guaranteed payment incentive arm was considered but not included because the primary methodological question is whether implementable, lower-cost alternatives can improve recruitment in a community platform context. To ensure the study still informs this design space, we will also assess nonparticipants' stated preferences for alternative incentive structures, including guaranteed payments (see Supplementary File S1).

The study has five objectives:

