To estimate the overall invitation-stage uptake for the proposed EMA study (i.e., the proportion of invitees who register interest) in this community recruitment context.To determine whether offering a financial incentive (eligibility for one of four £100 prize draws) or a social incentive (exclusive invitation to a neighbourhood social event for sharing study results) increases individuals’ willingness to participate in experience sampling research, compared with offering no incentive.To investigate whether the effectiveness of the incentives in promoting participation varies across demographic and residential subgroups, including residential status, age group, and gender.To examine the reasons provided for non-participation and assess whether the likelihood of endorsing specific reasons differs by incentive condition among those who declined participation.To identify which alternative incentives are most preferred by individuals who declined participation, and assess whether these preferences differ by the incentive condition originally offered.

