#### Secondary outcome variable

2.9.2

The study also assessed two secondary outcomes among participants who indicated that they were unwilling to participate in the EMA study. The first secondary outcome captured the reason for unwillingness to participate. Participants were asked to identify one or more factors influencing their decisions not to participate. These factors included (1 = “Inadequate compensation”), app notification frequency (2 = “Too many notifications”), study duration (3 = “long/excessive study duration”), limited time availability (4 = “daily time constraints”), app download (5 = “Reluctance to install new app”), privacy concerns (6 = “privacy and data security concerns”), lack of interest (7 = “Lack of interest in the study”), and [8 = Other reasons(please specify)]. Participants were asked to “select the main reason(s) for not participating in the future research study” from this list.

The second secondary outcome assessed alternative incentive preference. This outcome was obtained only for participants who selected “*Inadequate compensation”* as their main reason for non-participation. These participants were subsequently presented with a list of seven potential incentive alternatives they preferred to be offered for a similar study in the future. They were asked, “Would any of these increase your likelihood to participate? Check all that apply” The incentive options were: nothing (1 = “Nothing will increase my likelihood”), guaranteed cash payment (2 = “£50 guaranteed cash on study completion”), gift card (3 = “Gift card on study completion”), prize draw (4 = “4× £100 cash prize draw”), personalized feedback (5 = “Personalized well-being feedback”), special event invitation (6 = “Exclusive post-research social & feedback event”), charity donation (7 = “Donation to charity”), and other (8 = “Other—please specify”).

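### The alternative-incentive analysis has three different populations, and the one in section 2.12.4.2, read literally, selects on the outcome

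*Protocol article*

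**What the plan says.** The protocol article describes the population for this outcome in three ways.

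- **Introduction, objective 5:** "To identify which alternative incentives are most preferred by individuals who declined participation", and then to "assess whether these preferences differ by the incentive condition originally offered". The paragraphs before the objectives also promise nonparticipants' "stated preferences for alternative incentive structures, including guaranteed payments".
- **Section 2.9.2, Secondary outcome variable:** "This outcome was obtained only for participants who selected" inadequate compensation, one of eight coded reasons. The reasons question allowed several answers: "Participants were asked to identify one or more factors influencing their decisions not to participate". The first option in the preference list is "Nothing will increase my likelihood".
- **Section 2.12.4.2, Alternative incentives:** the analysis "will focus on participants who declined participation but indicated that specific alternative incentives might have increased their likelihood of taking part". The compensation filter is not mentioned. "Separate logistic regression models will be fitted for each alternative incentive option", with incentive condition as predictor and no incentive as reference.

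Two other places bear on the point. Section 2.10 reads as if every 'No' respondent gave incentive preferences. Section 2.11 says the follow-up preference items were optional. By contrast, the barriers analysis in section 2.12.4.1 has a clear set: those who select 'No'.

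**The concern.** The population decides what an endorsement percentage or an odds ratio means, and here it changes from section to section.

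The step from objective 5 to section 2.9.2 is a matter of scope. Decliners who cited only privacy, time, notifications or the app installation were never asked what might have changed their minds, so the objective as worded cannot be answered from the data.

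The step from section 2.9.2 to section 2.12.4.2 is a matter of analysis. Membership of the set depends on having endorsed a specific alternative, which is the outcome being analysed. A respondent who was asked and chose only the 'nothing' option is a valid non-endorser of every alternative, yet leaves the denominator.

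The result most exposed is the second half of objective 5, the comparison between arms. If the proportion who endorse anything differs by arm, the restriction alone can create or hide a difference for a given option. The Introduction also presents these answers as the way the study still informs the guaranteed-payment question after that arm was left out, so readers are likely to give them weight.

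**Working it through.** The article states no expected rate, sample size or power for this outcome, so there is no figure to reproduce. The check is algebra with assumed values.

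**Definitions (none of these values is in the article)**
- q = share of 'No' respondents who tick inadequate compensation and so are asked
- s = share of those asked who endorse at least one specific alternative
- e = share of those asked who endorse a given specific option

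**1. Effect of the restriction on proportions.** Everyone who endorses a given option is by definition in the restricted set, so the numerator is unchanged and the denominator is multiplied by s. The restricted rate is e / s. With e = 0.40 assumed:

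| s (assumed) | rate among those asked | rate in restricted set | factor 1/s |
|---|---|---|---|
| 1.0 | 40% | 40% | 1.00 |
| 0.9 | 40% | 44% | 1.11 |
| 0.8 | 40% | 50% | 1.25 |
| 0.7 | 40% | 57% | 1.43 |
| 0.5 | 40% | 80% | 2.00 |

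The factor is the same for every specific option, so their order does not change.

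**2. Effect on the arm comparison.** Assume 50 people are asked in each of two arms and 20 endorse a given option in each.
- Everyone asked: OR = (20/30) / (20/30) = 1.0.
- Now let 40 in the first arm and 25 in the second endorse at least one alternative (s = 0.8 and 0.5). The restricted set gives 20/40 versus 20/25, so OR = (20/20) / (20/5) = 0.25.

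The preferences for that option are identical in the two arms. The difference comes only from the denominator.

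**3. What can be said about all 'No' respondents.** The unasked share 1 − q could contain no endorsers or only endorsers, so the rate lies between q·e and q·e + (1 − q). With e = 0.40:

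| q (assumed) | lower bound | upper bound |
|---|---|---|
| 0.1 | 4% | 94% |
| 0.2 | 8% | 88% |
| 0.3 | 12% | 82% |
| 0.5 | 20% | 70% |
| 0.8 | 32% | 52% |

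The width is 1 − q whatever e is. No reanalysis narrows it, because the question was not put to the others.

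**The case against.** Several counter-arguments have force.

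- **Ranking and counts.** Section 2.12.4.2 plans endorsement frequencies, and the first half of objective 5 asks which options are most preferred. Dropping people who endorsed nothing changes neither the counts nor the order of the specific options. This stands, and it limits the damage to proportions and the between-arm models.
- **Inflation relative to all decliners.** A reader might infer that the percentages overstate what decliners in general want. That is plausible if people who cite compensation are more sensitive to incentives, but the article cannot establish it. It would be certain only if unasked decliners were counted as non-endorsers.
- **The 'nothing' option.** A reader might also infer that a regression on this option is planned and must be empty, or that the inflation equals 1/(1 − share ticking 'nothing'). Neither is secure. Section 2.9.2 speaks of seven alternatives but lists eight codes, so 'nothing' may not count as an alternative to be modelled. The item allowed multiple ticks with no stated exclusivity, and answering was optional. The quantity that matters is s.
- **Disclosure.** Section 2.9.2 states the branching openly, and the Discussion describes the results as coming from individuals who found the offered incentives unappealing. That narrows the claim in part, but objective 5 is not amended and the listed limitations omit the filter.
- **The separate analysis plan.** The opening verb in 2.12.4.2 may be loose wording, and section 2.12 refers to a detailed plan published elsewhere that may fix the denominator. That is possible, but objective 5, section 2.9.2 and section 2.12.4.2 of this article would still disagree with one another.

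**Conclusion.** The point holds as an internal inconsistency with an analytic consequence for an additional, non-primary outcome. Followed literally, section 2.12.4.2 conditions on the outcome. Relative to those asked, endorsement proportions rise by a factor 1/s, which is 1.11 to 2.0 for assumed s between 0.9 and 0.5 and exactly 1 only if every person asked endorsed some specific alternative. Between-arm odds ratios can be distorted when s differs by arm; the shift from 1.0 to 0.25 is an illustration with assumed counts, not a forecast.

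It does not follow that the ranking of options is wrong, or that the rates are inflated relative to all decliners; the latter is not identified. Nor does the Introduction call these data a replacement for the guaranteed-payment arm. It says only that they help the study inform that question.

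Correcting the analysis set does not make the arm comparisons randomized ones. Declining, and then citing inadequate compensation, both happen after randomization and may depend on what was offered.

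**What to change.** 1. In section 2.12.4.2, define the analysis set as all decliners shown the item, that is, those who selected inadequate compensation. Keep those who chose 'nothing' in the denominator and report 'nothing' as its own category.
2. Report by arm how many were shown the item and how many left it blank.
3. If all 'No' respondents are also used as a denominator, show the unasked as not asked and label the resulting figure a lower bound.
4. Reword objective 5, and any conclusion drawn from it, to refer to decliners who cited inadequate compensation. Align section 2.10 and the promise in the Introduction with that.
5. Label the between-arm comparisons for this outcome descriptive, because selection into the subset occurs after randomization.

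The survey closed on 30 November 2024, so the branching cannot be changed, but everything above can still be done with the data collected. The cost is a few sentences, a row for item non-response and, if wanted, one extra denominator column. The price in substance is a narrower claim.

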### Data management

2.11.

Several procedures were implemented to uphold data quality and ensure data security. The GMV survey design required responses for four core demographic items (gender, ethnic group, age range, and relationship to King's Cross), while follow-up preference items were optional. Additionally, the platform's device recognition feature guaranteed that once a participant submitted a response, they were unable to access the survey again, thereby preserving the uniqueness of each submission. As data were collected directly in a pre-coded digital format on the GMV platform, manual data entry was unnecessary, reducing the risk of transcription errors and enhancing the overall accuracy of the dataset.

The primary outcome—the participant's binary decision to participate (“Yes” or “No”)—was derived directly from the raw data exported from the GMV platform. Each survey response was coded post-collection: responses from participants who completed the “Yes” survey were assigned a value of 1 and those who completed the “No” survey were assigned a value of 0. This coding process ensured consistent and accurate representation of the primary outcome for analysis.

All data storage, handling, and sharing procedures will comply with institutional data security and ethical guidelines. Study data will be cleaned and anonymised prior to any sharing. Access to identifiable and cleaned study data will be restricted to authorised members of the research team and approved project partners in accordance with prior data-sharing agreements.

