#### Subgroup analyses

2.12.2.

Exploratory subgroup analyses will assess whether the effectiveness of the incentive conditions varies across demographic and residential subgroups. Interaction terms between incentive type (financial, social, or none) and participant characteristics (residential status, gender, and age group) will be included in the logistic regression models. These analyses will evaluate whether certain incentives are more effective for particular subpopulations, such as specific residential groups or demographic categories, thereby identifying potential differences in responsiveness across participant types.

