##### Analysis of barriers to participation

2.12.4.1.

The first additional outcome analysis will focus on participants who decline to participate in the EMA study (i.e., those who select “No”). Each potential barrier to participation will be represented as a binary variable indicating whether a given reason was endorsed. Descriptive statistics will summarize the frequency and percentage of each reported reason, stratified by incentive condition. Graphical summaries (e.g., bar charts) will be used to visualize the most frequently cited reasons and their distribution across incentive conditions.

To examine whether endorsement of specific barriers varies by incentive type, separate Firth logistic regression models will be fitted for each reason, with incentive condition (financial, social, or no incentive) as the main predictor. Firth logistic regression will be used to reduce sparse-data bias and to address potential separation. Odds ratios (ORs) and 95% confidence intervals (CIs) will be reported for each incentive condition relative to the no-incentive group, and False Discovery Rate (FDR) adjustment will be applied across the set of reason-specific models to account for multiple testing.

The total number of reasons endorsed by each respondent will be analyzed as a count outcome using Poisson regression. A model including incentive condition as the main predictor will be fitted to assess whether the number of reported barriers differs across the financial, social, and no-incentive conditions. Incidence rate ratios (IRRs) and 95% confidence intervals (CIs) will be reported.

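### The alternative-incentive models are planned as plain logistic regression, although the plan already uses Firth for the larger sample of decliners from which their respondents are drawn

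*Protocol article*

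**What the plan says.** All of this is in the protocol article.

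- **Reasons for declining (2.12.4.1).** The analysis "will focus on participants who decline to participate in the EMA study", and "separate Firth logistic regression models will be fitted for each reason". The justification is explicit: "Firth logistic regression will be used to reduce sparse-data bias and to address potential separation". The predictor is the three-level incentive condition. Odds ratios with 95% intervals are reported, and a false discovery rate (FDR) adjustment runs across the reasons.
- **Alternative incentives (2.12.4.2).** "Separate logistic regression models will be fitted for each alternative incentive option, with incentive condition (reference: no incentive) as the main predictor". The predictor, the 95% intervals and the type of FDR adjustment are the same. No penalisation or fallback is named.
- **Who was asked (2.9.2, Secondary outcome variable).** "This outcome was obtained only for participants who selected" inadequate compensation as their reason for declining.
- **Who is analysed (2.12.4.2).** The analysis "will focus on participants who declined participation but indicated that specific alternative incentives might have increased their likelihood of taking part". This is not the same definition as in 2.9.2.
- **Completeness (2.11, Data management).** Four demographic items were compulsory, "while follow-up preference items were optional".

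**The concern.** The plan recognises that data from active decliners may be too thin for ordinary maximum likelihood and protects against this for the reasons models. It then drops the protection for models of the same form fitted to a subset of the same people. Because Firth is named and justified immediately before, the plain term in 2.12.4.2 reads as unpenalised.

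With a three-level predictor and no other covariate, one arm in which nobody (or everybody) endorses an option is enough to cause separation. The maximum-likelihood log odds ratio for that arm then diverges, its standard error explodes and the Wald p-value goes to about 1. Objective 5 asks whether preferences differ by the incentive originally offered, and these models are the inferential answer to it. A pronounced difference between arms is one way an empty cell arises, so the method can fail where the contrast is strongest.

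**Working it through.** **1. Is the second sample nested in the first?** The reasons models use everyone who selected No. The alternative-incentive item was shown only to those among them who chose inadequate compensation (2.9.2). The second sample is therefore a subset, and optional items (2.11) can shrink it further. Section 2.12.3 also expects some uninterested invitees never to click No, which limits the starting sample.

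**2. Chance of separation for one option.** The article states no figure to reproduce and gives no number of decliners, no share citing inadequate compensation and no endorsement rates. All inputs here are assumptions. Take *m* respondents in each of three arms and a common endorsement rate *q*. One arm has a 0% or 100% cell with probability (1−q)^m + q^m, so

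P(at least one of three arms) = 1 − [1 − (1−q)^m − q^m]^3.

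Example with m = 10, q = 0.10: 0.9^10 = 0.3487 and 0.1^10 is negligible; 1 − 0.6513^3 = 0.72.

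| Respondents per arm | q = 10% | q = 20% | q = 30% |
|---|---|---|---|
| 5 | 93% | 70% | 43% |
| 10 | 72% | 29% | 8% |
| 20 | 32% | 3% | 0.2% |

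At 30 per arm the risk is 12% for q = 10% and 0.4% for q = 20%. At 60 per arm it is 0.5% for q = 10%.

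**3. Full decliner sample against the subset, same q.**

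| Assumed decliners and share asked | Per arm: reasons vs alternatives | q = 5% | q = 10% |
|---|---|---|---|
| 150, 20% | 50 vs 10 | 21% vs 94% | 1.5% vs 72% |
| 300, 20% | 100 vs 20 | 1.8% vs 74% | <0.1% vs 32% |
| 600, 30% | 200 vs 60 | <0.1% vs 13% | <0.1% vs 0.5% |

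At equal endorsement, the subset's risk is never below that of the full sample. It is negligible only for large subsets or common options.

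**4. What a separated fit returns.** Invented data with 10 per arm: 6 endorsements in control, 0 in financial, 5 in social. Financial against control:

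- Maximum likelihood: log OR about −23, SE about 15,000, Wald p = 0.999.
- Firth: log OR −3.41, penalised likelihood-ratio p = 0.003.
- Fisher's exact test, for reference: p = 0.011.

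The default Wald output turns a strong contrast into a p-value of about 1.

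**5. Effect on the other options.** The number of tests in the FDR step does not change. Replacing one p-value by a value near 1 can only raise the other options' adjusted p-values or leave them as they are.

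**6. The analysis set.** Read literally, 2.12.4.2 keeps only those who said some alternative might help. That selects on the outcomes being modelled, and it removes anyone whose only answer was that nothing would help, although that answer is one of the eight coded options. Section 2.9.2 implies the wider set of everyone who was asked. Firth does not settle which denominator applies.

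**The case against.** The strongest objection is that the article refers to a separate, detailed statistical analysis plan (2.12) and never uses the words ordinary or maximum likelihood. The estimator may be settled there. That stands as a caution. It does not remove the point, because the article itself fixes an estimator in both sections and fixes them differently.

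It is also fair to say that the small counts are assumed. Respondents who have just cited inadequate compensation may often tick cash or gift cards, so sparsity would concentrate in less popular options. Likewise, a very rare reason in 2.12.4.1 could be sparser than a popular incentive. The comparison therefore holds at equal endorsement rates, not for every pair of models.

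Three stronger readings are tempting, and the document does not support them:

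- **The subgroup models share the fault.** Section 2.12.2 says that interaction terms "will be included in the logistic regression models", also without Firth. But those models are not confined to decliners, and the plan does not use Firth for the primary model either, so there is no inconsistency. For the 541 residents (about 180 per arm), the chance that at least one arm has no Yes is 1 − (1 − (1−p)^180)^3: 42% at 1% uptake, 8% at 2%, 1.2% at 3% and 0.03% at 5%. It is material only at the very bottom of the article's 1% to 70% range, in analyses labelled exploratory.
- **A separated option corrupts the whole FDR step.** Its effect on the other options is at most conservative (step 5).
- **Section 2.12.4.1 is already a complete template.** It names Firth but not the type of interval or test, so both sections need that detail.

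**Conclusion.** The inconsistency is real and minor. As worded, 2.12.4.2 leaves out a safeguard that 2.12.4.1 adopts for a larger sample containing the same respondents. The size of the risk depends on counts the article does not give: roughly 30% to 70% per option at 10% endorsement with 20 down to 10 respondents per arm, and under 1% by 60 per arm. These figures assume equal arms and a common endorsement rate.

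The harm falls on the affected option's own odds ratio, interval and p-value, and so on the between-arm part of objective 5. The descriptive frequencies, which show which alternatives are most preferred, and the primary comparison of willingness are untouched.

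**What to change.** - In 2.12.4.2, fit each alternative-incentive option by Firth logistic regression, as 2.12.4.1 does for each reason.
- In both sections, state that intervals are profile penalised-likelihood intervals and that the p-values entering the FDR step come from penalised likelihood-ratio tests.
- In 2.12.4.2, define the analysis set to match 2.9.2: all decliners who were asked the item and answered it, including those who said nothing would help. Report that denominator by arm.
- If the separate analysis plan already names Firth for these models, align the article with it.

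No change to the subgroup models is needed on this ground. The cost is a few lines of wording: the method is already in the plan, no new data are needed, and little is lost if the data turn out not to be sparse.
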